### Sample size calculation

There are no meaningful rules of thumb to estimate the sample size needed for a mixed models analysis, because, with random and fixed effects estimations, too many factors of uncertainty are involved. Therefore, a standard sample size calculation with a correction for the design effect based on the intercorrelation was used.

These calculations were performed in SPSS version 20.0 using the mixed-model ANOVA procedure as described by Aberson [39]. Type 1 error (alpha) was set at 0.05, and power (1-beta) on 0.80.

To estimate the effect size and correlation we analysed data of a natural cohort collected by one of the authors ([name]) containing general features of keloid patients and POSAS values before and after treatment with intralesional cryotherapy. This natural cohort contains measurements at baseline, and at 12, 26, and 52 weeks after treatment. It comprised POSAS observer values from one or two observers and patient values; however, many patients lacked values for some time points (56% of follow-up complete). Only a small amount of items were missing, in total 15/3378 (0.44%) items of the POSAS data were imputed following the rules described previously.

The assumed medium-sized effect of 0.5, based on a SD of around 15 (Table 1), corresponds to 7.5 points on the POSAS scale; this is slightly more than the 6 points that is regarded as a clinically significant difference. We assumed a correlation of 0.75 between time points; this was difficult to verify in the data of the natural cohort because of many incomplete cases.

**Table 1 T1:** Descriptive statistics

	**N**	**Minimum**	**Maximum**	**Mean**	**SD**
POSAS baseline	73	30	93	60.45	12.276
POSAS 12 wk post op	44	18	85	50.65	15.474
POSAS 26 wk post op	46	17	83	49.23	15.854
POSAS 52 wk post op	33	24	81	46.18	13.959
POSAS overall	196	17	93	53.32	15.20

POSAS, Patient and Observer Scar Assessment Scale score; post op, postoperative.

wk, weeks.

The analysis, based on the observed SD and expected correlation and effect size, resulted in a group size of 33 patients, taking into account a 25% loss to follow-up and the four treatment groups; this results in a total sample of 176 subjects.

No interim analysis is planned because we do not expect any severe side-effects and, by the time a sufficient part of the participants has finished follow-up, almost all participants will have had their intervention. No rules related to stopping/withdrawal from the study have been specified.

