## Discussion

We have described a trial protocol; this is becoming standard practice when conducting clinical trials, although surgical trials are somewhat behind medical trials. The importance of publishing an extensive protocol is that it addresses questions (that may not be answered in the Methods section due to limited space) that might arise on how the trial was organised after publication of the results. It also prevents publication bias due to inconclusive or negative results. This will be the first randomised controlled trial comparing surgical keloid treatments using validated PROMs.

We have presented the problems with power analysis and sample size calculations for a more complex but sophisticated statistical model. In this corrected analysis we did not rely on assumptions only, but used previously collected data to determine the effect size and intercorrelation. The effect size we have chosen is a conservative one in order to ensure clinical relevance. When the effect size appears in fact to be smaller, we expect to be underpowered. Due to the quantity of work involved in logistics and data collection, we made this decision despite the risk of a negative result.

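### The 80% power depends on a correlation of 0.75 that the protocol article calls assumed in one section and determined from data in another, and on a 25% loss with no stated basis

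*Protocol article*

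**What the plan says.** Sample size calculation: the design targets are given as "Type 1 error (alpha) was set at 0.05, and power (1-beta) on 0.80". The effect is described this way: "The assumed medium-sized effect of 0.5, based on a SD of around 15 (Table 1), corresponds to 7.5 points on the POSAS scale". The section says that a cohort treated with intralesional cryotherapy was analysed to estimate the effect size and correlation, but then reports of the correlation: "We assumed a correlation of 0.75 between time points; this was difficult to verify in the data of the natural cohort". The reason it gives is the number of patients with gaps in their data. Its closing summary calls the SD observed, and the correlation and effect size expected. On the cohort's completeness it says: "however, many patients lacked values for some time points (56% of follow-up complete"). Table 1 gives 73 POSAS values at baseline and 44, 46 and 33 at weeks 12, 26 and 52. The result is 33 per group, which becomes 176 after "taking into account a 25% loss to follow-up and the four treatment groups".

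Discussion: the calculation is said not to rest on assumptions alone, because the authors "used previously collected data to determine the effect size and intercorrelation". The one risk to power mentioned there is an effect smaller than planned.

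Statistical analysis: a linear mixed model that can use patients with missing visits. The candidate covariates named are sex, age, skin type, duration and location; baseline POSAS is not among them.

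**The concern.** The two sections give different origins for the same inputs. By the wording of Sample size calculation, only the SD was observed. A reader of the Discussion would conclude that the effect size and the correlation were measured too. For the effect size this could not be so in the sense that matters: the cohort had one treatment, so it holds no difference between treatments.

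The correlation is not a minor input. It cuts the required group size by about half, so how well it is supported decides how far the 80% can be trusted. The 25% loss likewise has no source, and the only follow-up data cited are less complete. At stake is how a null result would be read. If the correlation is lower or the missingness higher than planned, a non-significant comparison says less than the stated power suggests, and the Discussion warns of neither.

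**Working it through.** **Inputs.** From Sample size calculation: alpha 0.05 (two-sided assumed, as sidedness is not stated), power 0.80, difference 7.5 points, SD 15, correlation ρ = 0.75, loss 25%, four groups. From Table 1: SD 12.276 at baseline and 13.959 at week 52; N = 73, 44, 46, 33.

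**1. Reproducing the plan's figure.** For a two-group comparison of change from baseline:

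- SD of change = 15 × √(2(1 − 0.75)) = 10.61
- standardised effect = 7.5 / 10.61 = 0.707
- noncentral t: 33 per group, power 80.8%
- 33 / (1 − 0.25) = 44; 44 × 4 = 176

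This matches exactly. Other forms at the same inputs do not: 64 per group with no correction for correlation, 29 with baseline as a covariate (SD 15 × √(1 − 0.75²) = 9.92), and 52 to 54 for the mean of three to five measurements. The change-score form is therefore inferred from the match; the article does not state it.

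**2. Sensitivity to the correlation.** The Table 1 column uses SD of change = √(12.276² + 13.959² − 2ρ × 12.276 × 13.959), which is 9.41 at ρ = 0.75 and 10.28 at ρ = 0.70. The three power columns are for 33 per group and 7.5 points.

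| ρ | Change score, SD 15 | Change score, Table 1 SDs | Baseline as covariate, SD 15 | n per group for 80% (change, SD 15) | Total at 25% loss |
|---|---|---|---|---|---|
| 0.75 | 81% | 89% | 86% | 33 | 176 |
| 0.70 | 73% | 83% | 80% | 39 | 208 |
| 0.60 | 61% | 72% | 71% | 52 | 280 |
| 0.50 | 52% | 62% | 64% | 64 | 344 |

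**3. Follow-up in the cohort.** (44 + 46 + 33) / (3 × 73) = 123 / 219 = 56.2%, the article's 56%. By visit: 44/73 = 60%, 46/73 = 63%, 33/73 = 45%.

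**4. What such missingness would mean in the trial, at ρ = 0.75 and SD 15.** A complete-case change score with 44 × 0.56 = 24.6 per group has 68% power; with 44 × 0.452 = 19.9 per group it has 58%. The planned analysis is a mixed model, so these are pessimistic. For a mixed model I took 44 per arm, baseline complete, each follow-up visit observed at the cohort's rate independently of the others, and equal correlation between visits. The standard error of the week-52 contrast is then 3.08 points with separate baseline means (power 68%) and 2.98 points with a common baseline mean (power 71%).

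**The case against.** The strongest reply is that nothing was miscalculated, and that Sample size calculation is itself open about which inputs were observed and which were expected. That is right. A reader might infer that the sample size is wrong; the exact reproduction of 33, 44 and 176 rules that out. A reader might also infer that the correlation cannot be checked; the article says only that checking was difficult. The fault on this part lies in one Discussion sentence and in the missing caveat.

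Second, a reader might infer that the cohort contradicts the 25%. It does not. The 56% counts visit values present in an uncontrolled cohort, not patients retained. More patients have a value at week 26 (46) than at week 12 (44), so some of the gaps are intermittent, and the article does not say whether all 73 had reached week 52. The trial has scheduled visits and online questionnaires. What stands is that 25% is given without a source and is more favourable than the only data cited.

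Third, the loss of power depends on the contrast and the SD. With the Table 1 SDs, power is still 83% at a correlation of 0.70. If the effect were a constant 7.5 points and the contrast were the average over follow-up in the mixed model of step 4 with a common baseline mean, power would be about 97% at 0.75 and 86% at 0.50 even with cohort-like missingness. The article fixes no such contrast, and the form that reproduces its 33 is the change score. So the figures are conditional, but the dependence on the correlation in the plan's own calculation is not in doubt.

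Finally, the Discussion does accept a risk of low power, but only for a smaller effect. Correlation and loss remain uncovered.

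**Conclusion.** The point holds as a conflict between two sections and as unsupported inputs. The Discussion misdescribes the basis of the calculation: effect size and correlation were assumed, and only the SD came from the cohort. The assumed correlation takes the requirement from 64 to 33 per group. In the form that reproduces the plan, power falls from 81% to between 73% and 52% as the correlation goes from 0.75 to between 0.70 and 0.50; with the Table 1 SDs the fall is from 89% to between 83% and 62%. With missingness like the cohort's, a mixed model would have about 68% to 71% power at week 52 even at a correlation of 0.75.

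These sizes rest on a two-sided 5% test, a true difference of 7.5 points, the inferred change-score form and, for the last figure, missingness independent across visits. They do not show that the trial is underpowered, because the true correlation and the trial's own loss are unknown.

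**What to change.** 1. Correct the Discussion to say that the SD came from the cohort and that effect size and correlation were assumed.
2. State the 80% as conditional on a correlation of 0.75 and 25% loss. Give a basis for the 25% and a sensitivity range over both inputs, for example correlations from 0.50 to 0.75 and week-52 missingness from 25% up to the cohort's 55%. Estimate the correlation from whatever cohort pairs exist (at most 33 for baseline and week 52; the actual number is not reported) and report it with its uncertainty.
3. Adjust the primary mixed model for baseline POSAS: either as a covariate with only follow-up values as outcomes, or as an outcome with a common baseline mean across arms, but not both. In the single-visit calculation at 33 per arm this raises power from 81% to 86% at a correlation of 0.75, and holds 80% at 0.70.

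Cost: a corrected sentence, a restated power figure, one re-analysis of data already held, and a covariate already collected. No extra patients are needed. The downside is a less favourable stated power.

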### Ethical issues

The risks of undergoing surgical treatment include complications due to undergoing anaesthesia and surgery; however, these risks are equivalent to the risks of surgical treatment without participating in the study. Only patients not responsive to conservative treatment and who opt for surgical treatment, despite knowing the risks, are enrolled in the trial.

Anticipated benefit for the medical world is improved outcome for future patients. The results will improve decision making, helping evidence-based guidelines to be developed for keloid treatment. We aim to determine the place of intralesional cryotherapy in the ‘stepped- care approach’ (that is, whether it should be used as second step, be added as an extra step, or has no place at all in the treatment of keloids). If cryotherapy is shown to be effective for resistant keloids, then savings can be made by avoiding the costly brachytherapy treatment. If cryotherapy is not effective, the patient will receive appropriate treatment sooner.

### Time frame

We will include patients over a period of 2.5 years and will follow every patient for one year, resulting in a total study period of 3.5 years.

## Discussion

We have described a trial protocol; this is becoming standard practice when conducting clinical trials, although surgical trials are somewhat behind medical trials. The importance of publishing an extensive protocol is that it addresses questions (that may not be answered in the Methods section due to limited space) that might arise on how the trial was organised after publication of the results. It also prevents publication bias due to inconclusive or negative results. This will be the first randomised controlled trial comparing surgical keloid treatments using validated PROMs.

We have presented the problems with power analysis and sample size calculations for a more complex but sophisticated statistical model. In this corrected analysis we did not rely on assumptions only, but used previously collected data to determine the effect size and intercorrelation. The effect size we have chosen is a conservative one in order to ensure clinical relevance. When the effect size appears in fact to be smaller, we expect to be underpowered. Due to the quantity of work involved in logistics and data collection, we made this decision despite the risk of a negative result.

## Trial status

At the time of submission of this protocol (August 2013), this study was recruiting patients to participate in the study.

## Abbreviations

POSAS: Patient and Observer Scar Assessment Scale; PROM: Patient Reported Outcome Measure; QoL: Quality of life; SD: Standard deviation; SF-36: World Health Organisation Quality of Life assessment Short Form-36.
